### Randomization

Participants will be randomized using computer-generated randomization to either the intervention group or the control group (1:1). Randomization will be stratified by site and restricted using permuted random blocks within each strata. The random allocation sequence will be implemented using the REDCap study database by a biostatistician unaffiliated with the study. This biostatistician will generate the random allocation sequence to assign participants to either the intervention or control groups. No one directly involved in the study will have access to the allocation sequence and this feature will be accessed exclusively by the unaffiliated biostatistician. The pre-determined allocation sequence from the biostatistician will be employed centrally (FMC) to assign participants to the intervention or control group. Research assistants will receive this information from the REDCap database once a patient is consented.

### Blinding

Due to the nature of the intervention, participants, care providers, and study staff will not be blinded to the intervention. The individuals collecting data and conducting the data analysis will be blinded to the assignment of interventions.

### Study intervention

Participants in both the intervention and control groups will receive an informational pamphlet developed by our team on ICU delirium (standard of care); this will be presented to all patients and families upon admission. In addition to the pamphlet, the intervention is comprised of two components: (1) an education module for family members to prevent, detect, and manage ICU delirium; and (2) delirium detection using the Sour Seven [41], a validated family member-administered ICU delirium detection tool [42]. Family members are not engaged in the assessment of delirium in usual care. To ensure consistency between patients, the study team will use a standardized wording to introduce the study and to answer common questions.
Education: Our team developed and pilot tested the educational materials, both paper (i.e., booklet) and digital (i.e., https://youtu.be/I88-Lohht64) formats, which included a video, hypothetical case vignettes, and a delirium knowledge questionnaire. We created the educational video with input from patients, family members, and members of the ICU care team. In addition our team modified an existing Caregiver Delirium Knowledge Questionnaire [43] to the ICU context to develop the Caregiver ICU Delirium Knowledge Questionnaire (CIDKQ) [44]. We developed case vignettes of hypothetical ICU patients based on the four features that, when found in combination, indicate delirium is present: sudden onset or fluctuating course AND inattention AND either altered level of consciousness OR disorganized thinking. **The CIDKQ** (Cronbach alpha = 0.80) and case vignettes (Sour Seven Sensitivity: 90.0%, Specificity: 65.0%) were validated in a cross-sectional study of 80 family members [44]. The **educational materials were validated** in a **quasi-experimental pre-test post-test study to validate** the education materials. Preliminary results demonstrate improvement in family member delirium knowledge after receiving delirium education (as measured by the CIDKQ) and improvement in identification of delirium in hypothetical ICU patients (Sour Seven Sensitivity: 100.0%, Specificity: 75%). This education module will be presented to family members on the signs of delirium, risk factors, delirium detection, and delirium prevention and management using non-pharmacological strategies. The material will be provided as a 6-min video or as a booklet. Family members will practice identifying delirium with the Sour Seven, using previously validated case vignettes of hypothetical ICU patients [44]. The education module will be provided on day one of the study by a patient advisor or research assistant.**Family-administered delirium prevention, detection, and management:** Our team completed a **systematic review** to identify existing family member-administered delirium detection tools [45], which included the Family Confusion Assessment Method (FAM-CAM) [46] and Sour Seven [41] **and an observational study** of 147 patient-family member dyads by our team evaluated the reliability and validity of the FAM-CAM [46] and Sour Seven [41] in the ICU [39, 42]. The Sour Seven had superior diagnostic accuracy [(Sour Seven Sensitivity: 72.9%, Specificity: 68.8%) (FAM-CAM- Sensitivity: 54.1%, Specificity: 76.8%)], with family members preferring the Sour Seven and thus, the Sour Seven will be employed in the current study [39].For up to five study days, family members will be provided a daily checklist of non-pharmacological interventions to prevent and manage delirium, which include patient orientation (e.g., noting date, time, and location), mobility (e.g., family-assisted mobility), and environmental protocols (e.g., providing glasses or ear plugs). They will complete the Sour Seven once daily to detect delirium in the patient.

### Timing of intervention

The first day of intervention materials will be provided to the family upon enrollment (Fig. 1). The family will be provided ICU delirium education either by watching a 6-min video on their personal device or on a study tablet. If preferred, the family caregiver can receive the education by reading through a physical delirium education booklet with the research assistant or patient advisor (to ensure standardized provision of delirium education). Following the delirium education, the family will use the information contained in two case vignettes to practice completing the Sour Seven. Demographic questionnaires for the patient and family member will be administered on day one of the study. Knowledge of delirium on the CIDKQ [44] will be assessed prior to the intervention and immediately following administration of the education module. Delirium prevention and management strategies utilized by the family will be queried once daily (for 5 days maximum). The burden of delirium (Delirium Burden Scale [DEL-B]) on caregivers will be assessed daily for up to 5 days. Family delirium detection assessments (Sour Seven) will be conducted once daily over the course of the ICU stay (maximum 5 days). The results of the family delirium assessments will be shared with the bedside nurse by the research team. Family member psychiatric symptom assessments (Patient Health Questionnaire-9 [PHQ-9] and Generalized Anxiety Disorder-7 [GAD-7]) and distress (Kessler Psychological Distress Scale [K-10]) will be conducted daily over the course of the ICU stay (maximum of 5 days), with the distress and psychiatric questionnaires completed BEFORE the Sour Seven questionnaire is completed. Questionnaires on the caregiver’s ICU experience (Critical Care Family Needs Inventory [CCFNI]; Barriers to Care Questionnaire [BCQ]) and coping strategies (Coping Strategies Scale [CSS]), will be completed once over the course of the ICU stay (day 1).

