#### Secondary aims

To determine the effect of family-administered delirium prevention, detection, and management in critically ill patients on family member symptoms of psychological distress, compared to usual care.To determine the effect of family-administered delirium prevention, detection, and management on the prevalence (ever/never delirium as indicated by an Intensive Care Unit Delirium Screening Checklist [ICDSC] score ≥ 4), duration (total days of an ICDSC score ≥ 4), and severity of delirium (as indicated by the ICDSC score, which ranges from 0 to 8) in critically ill patients, compared to usual care.To determine the effect of family-administered delirium prevention, detection, and management on the diagnosis of the patient with delirium (ICDSC score ≥ 4), compared to usual care.To determine the effect of family-administered delirium prevention, detection, and management on family member knowledge of delirium in critically ill patients, compared to usual care.To determine the effect of family-administered delirium prevention, detection, and management on the burden of delirium (e.g., feelings of helplessness) experienced by family members of critically ill patients, compared to usual care.

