#### Patient outcomes

##### Intensive Care Delirium Screening Checklist (ICDSC)

The ICDSC is an 8-item, delirium assessment tool for use in the ICU (1 point per item) [4]. An altered level of consciousness, along with the presence of three other symptoms, including inattention, psychomotor agitation/retardation, and disorientation are required to diagnose delirium. Scores of ≥4 out of 8 on the ICDSC are indicative of delirium (Sensitivity: 99%; Specificity: 64%) [4]. The ICDSC yields both a continuous measure of symptoms and a dichotomous diagnosis of delirium. The ICDSC is completed twice daily by on-duty bedside nurses as part of standard care.

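### In the intervention arm only, the unblinded nurse who scores the ICDSC is given the family's Sour Seven result, so a null or higher ICDSC result for secondary aim 2 could not be separated from better detection

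*Protocol article*

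**What the plan says.** All references are to the protocol article.

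- **Study intervention:** daily family use of the Sour Seven is one of the two intervention components. For the comparator, "Family members are not engaged in the assessment of delirium in usual care".
- **Timing of intervention:** the Sour Seven is done once daily for at most five days, and "The results of the family delirium assessments will be shared with the bedside nurse by the research team".
- **Intensive Care Delirium Screening Checklist (ICDSC):** "The ICDSC is completed twice daily by on-duty bedside nurses as part of standard care".
- **Blinding:** "participants, care providers, and study staff will not be blinded to the intervention". The same section adds: "The individuals collecting data and conducting the data analysis will be blinded to the assignment of interventions".
- **Secondary aims:** aim 2 defines prevalence as "ever/never delirium as indicated by an Intensive Care Unit Delirium Screening Checklist" at a score of 4 or more, and takes duration and severity from the same instrument. The Statistical analysis plan section adds delirium-free days, also on the ICDSC.
- **Aim 3** is worded in Secondary aims with the same ICDSC threshold. The Statistical analysis plan and Sample size calculation sections instead take it from the medical chart.

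**The concern.** This goes beyond the usual lack of blinding in a behavioural trial. The person who scores the patient outcome receives, in one arm only, a daily prompt about that same outcome.

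The plan expects two effects that push recorded delirium in opposite directions. The Background hypothesises shorter and less severe delirium through prevention and management. It also says that most cases go unrecognised and that families may notice changes first, and the trial is sized on charted delirium rising. If the nurse's ICDSC responds to the family's result, a real reduction in delirium could be partly or wholly hidden, and an absence of effect could look like an increase. Prevalence (ever/never) and severity (worst score) are the more exposed, because a single raised reading can change them.

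What is at stake is the interpretation of secondary aim 2.

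**Working it through.** **Step 1. Is the link real?** Four statements are needed, and each is in the article.

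1. The Sour Seven is used in the intervention arm only (Study intervention). The article does not say in so many words that hand-over is confined to one arm; it follows because control families make no assessment to hand over.
2. The result goes to the bedside nurse (Timing of intervention).
3. The bedside nurse scores the ICDSC and, as a care provider, is not blinded (ICDSC; Blinding).
4. The ICDSC defines all aim 2 outcomes (Secondary aims; Statistical analysis plan).

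Table 2 names a research assistant for the ICDSC, but marks it as having no case report form. The Study design section describes delirium measures as routinely collected in the bedside system. The natural reading is that the assistant extracts the nurse's score. Blinding those who collect the data cannot help once the score has been set. The pre-post comparison does not help either, because the change in ascertainment begins after baseline. No independent delirium rating is described.

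**Step 2. The plan's own figure.** The plan gives none for an effect of hand-over on the ICDSC. Its one detection figure is the sample size for charted delirium (10% to 30%, 90% power, two-sided 0.05, 20% loss):

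n = (1.960 + 1.282)² × (0.10 × 0.90 + 0.30 × 0.70) / 0.20² = 10.51 × 0.30 / 0.04 = 78.8, so 79; 79 / 0.80 = 98.75, so 99 per group.

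This reproduces the stated 99 and is not in dispute. It shows that recognition is expected to rise.

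**Step 3. How differential ascertainment acts.** For true share p, nurse sensitivity Se and specificity Sp:

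measured share = p × Se + (1 − p) × (1 − Sp)

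Assumptions: one classification per patient; p = 50% in control (the Background says over half); a true fall to 40% where an effect is supposed; Sp = 90%.

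| Intervention-arm scenario | Control measures | Intervention measures | Difference (points) |
|---|---|---|---|
| True 40%, Se stays 50% | 0.25 + 0.05 = 30% | 0.20 + 0.06 = 26% | −4 |
| True 40%, Se 50% to 60% | 30% | 0.24 + 0.06 = 30% | 0 |
| True 40%, Se 50% to 70% | 30% | 0.28 + 0.06 = 34% | +4 |
| No effect, Se 50% to 60% | 30% | 0.30 + 0.05 = 35% | +5 |
| No effect, Se 50% to 40% | 30% | 0.20 + 0.05 = 25% | −5 |
| True 40%, Se 70% to 85% | 0.35 + 0.05 = 40% | 0.34 + 0.06 = 40% | 0 |

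**Step 4. At the ICDSC accuracy the article cites (99% / 64%).** Control measures 0.495 + 0.18 = 67.5%.

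- With no true effect, raising Se to 100% gives 0.50 + 0.18 = 68.0%, only +0.5 points. Better sensitivity has almost no room to act.
- With a true fall to 40% and no change in scoring, the intervention arm measures 0.396 + 0.216 = 61.2%, a difference of −6.3 points.
- Now suppose nurses act on a positive family result half the time, with independent errors (both assumed), at the article's Sour Seven accuracy of 72.9% / 68.8%. Se = 0.99 + 0.5 × 0.01 × 0.729 = 0.9936. Sp = 0.64 − 0.5 × 0.64 × 0.312 = 0.5402. The arm measures 0.40 × 0.9936 + 0.60 × 0.4598 = 67.3%, against 67.5% in control. The true fall is nearly hidden, this time by false positives.

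**Step 5. What is missing.** Every row depends on how often a nurse changes an ICDSC score because of the family's result. The documents give no such rate.

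**The case against.** The case against a stronger claim is good, and most of it stands.

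- **Direction.** A reader might infer that the bias can only run upward. The documents do not support that. At 72.9% sensitivity, 27.1% of delirious patients send the nurse a negative result, which could reassure and lower a score. Upward is the more likely direction, because a positive result prompts a second look, but it is not established.
- **Interpretability.** A reader might infer that aim 2 cannot be interpreted at all. That goes too far. If the bias is upward, a measured fall is conservative and still points to benefit. The ambiguity lies in a null or an increase.
- **Undetected cases.** The Background statement about missed cases concerns screening programmes worldwide, not ICDSC scoring in these four units. At the cited 99% sensitivity there is little left to detect.
- **Size.** It is tempting to build an inflation figure from the Sour Seven specificity and the Background prevalence. That prevalence is a share of admitted patients, not a daily rate. The step from a false positive family result to a raised ICDSC has no source. With a cited ICDSC specificity of 64%, many such patients would already score 4 or more.
- **One score for two aims.** The ICDSC wording of aim 3 might suggest that detection and occurrence are both read from one score. The analysis and sample size sections use the chart, so this is a wording mismatch.
- **Remedy.** Basing the main analysis on pre-hand-over readings would halve the data on a fluctuating condition. From day 2 every reading still follows an earlier hand-over, and the day 1 reading before hand-over is essentially a baseline.

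What survives is the chain itself: nothing in the article addresses the differential ascertainment.

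**Conclusion.** The concern holds in a limited form. By design, delirium is ascertained differently in the two arms for all of secondary aim 2, probably but not certainly upward in the intervention arm. A null or higher ICDSC result there could not be separated from better detection. A clear measured fall would still suggest benefit, on the working assumption that the bias is upward.

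The primary PHQ-9 and GAD-7 outcomes are not affected by this route. For charted diagnosis, better detection is the intended effect, not a bias.

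The size cannot be computed from the documents. The illustrations show only that moderate changes are enough: under the assumptions stated, a 10-point gain in nurse sensitivity (50% to 60%) removes a true 10-point fall, and with no true effect it adds 5 points. The point merits correction but does not threaten the trial's primary conclusion.

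**What to change.** 1. **Time-stamp each Sour Seven hand-over** to the bedside nurse. The hand-over itself need not change.
2. **Keep all routine ICDSC readings as the main aim 2 analysis**, and pre-specify a sensitivity analysis that uses the ICDSC charted before that day's hand-over, matched to the same shift in control. State that carry-over from earlier days remains from day 2.
3. **State what aim 2 can show.** Suggested wording: *Aim 2 estimates combine the occurrence of delirium with its detection by bedside nurses, who receive family assessments in the intervention arm only. A null or higher ICDSC result in that arm will be treated as inconclusive about occurrence: it will be neither taken as evidence of harm nor dismissed in advance.*
4. **Reword aim 3 in Secondary aims** from the ICDSC threshold to the medical-chart diagnosis used in the Statistical analysis plan and Sample size calculation sections.

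The cost is one extra data field, a little more analysis and a more modest claim for aim 2. A delirium rating made alike in both arms by someone who has not seen the family's result would separate detection from occurrence more directly, but it would need additional assessments that the article does not provide for.

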**Fig. 1 Fig1:**
[figure not shown]
CONSORT Flow Diagram

#### Study follow-up

Follow-up of family members will occur at 1- and 3-months post-ICU discharge (Fig. 1). Our team has developed a secure, online survey site for questionnaire completion. For participants who prefer paper forms, a pre-addressed stamped envelope with questionnaires will be provided. We will send reminders to participants 1-week prior to the follow-up date, and continue to provide reminders up to 1-week following the follow-up date.

### Measurement of exposures

#### Caregiver ICU delirium knowledge questionnaire (CIDKQ)

The CIDKQ is a 21-item questionnaire to assess a caregiver’s delirium knowledge (e.g., risk factors, outcomes and symptoms). The questionnaire will be completed on day one of the study before and immediately after the education module, and at 1-month and 3-month follow-up post patient ICU discharge.

#### Sour Seven

The Sour Seven is a 7-item tool to detect delirium based on the Diagnostic and Statistical Manual of Mental Disorders (DSM) criteria [2] for delirium in patients, including those with dementia, and is designed to be administered by family members [41]. Assessed symptoms include reduced attention, an altered level of awareness, and disordered thinking. Scores of ≥9 out of 18 are indicative of delirium [41]. The questionnaire will be completed once daily for up to five study days.

#### Critical Care Family Needs Inventory (CCFNI)

The CCFNI is a 45-item tool that identifies caregiver needs across five domains: assurance, proximity, information, comfort, and support [47, 48].

#### Barriers to Care Questionnaire (BCQ)

The BCQ is a 39-item tool that assesses caregiver barriers regarding health knowledge and beliefs, expectations about care, skills, and marginalization [49]. Scores range from 0 to 100, with higher scores indicating fewer barriers [50].

#### Coping Strategies Scale (CSS)

The CSS is a 48-item questionnaire that assesses a caregiver’s coping strategies in response to stress caused by health-related issues [51].

#### Richmond Agitation and Sedation Scale (RASS)

The RASS is a 10-point agitation-sedation scale centered at 0 (indicates calm and alert), with scores ranging from + 4 to − 5; more negative scores indicate greater levels of sedation and more positive scores indicate higher levels of agitation [52]. The RASS score is completed by on-duty bedside nurses as part of standard care every 4 h.

### Measurement of outcomes

#### Family member outcomes

##### Generalized Anxiety Disorder-7 (GAD-7) (primary aim)

The GAD-7 is a validated 7-item scale following the DSM criteria for generalized anxiety disorder (GAD) over the previous 2 weeks [53]. Scores of ≥10 out of 21 are indicative of clinically significant GAD [53]. The questionnaire will be completed by caregivers (assessing their symptoms) once daily for up to five study days, and at 1-month and 3-month follow-up post patient ICU discharge.

##### Patient Health Questionnaire (PHQ-9) (primary aim)

The PHQ-9 is a validated 9-item scale for assessing symptoms of major depression in the past 2 weeks, based on DSM criteria for depression [54]. Scores of ≥10 out of 27 indicate clinically significant depression [54]. The questionnaire will be completed by caregivers (assessing their symptoms) once daily for up to five study days, and at 1-month and 3-month follow-up post patient ICU discharge.

##### Kessler Psychological Distress Scale (K-10) (secondary aim 1)

The K-10 is a 10-item tool to measure psychological distress and the likelihood of having a mental disorder [55] with higher scores indicating greater psychological distress. The questionnaire will be completed by caregivers (assessing their symptoms) once daily for up to five study days, and at 1-month and 3-month follow-up post patient ICU discharge.

##### Delirium Burden Scale (DEL-B) (secondary aim 5)

The DEL-B is an 8-item tool with two-level questions; the first level lists delirium burden features and if answered positive (yes), the follow-up question asks caregivers to rate how distressing the burden (e.g., feelings of helplessness, concern about increased responsibilities, not being recognized by patient) was on a 0–4 scale [56]. Total scores range between 0 and 40, with higher scores indicative of greater burden [56]. The DEL-B will be completed once daily for up to five study days.

#### Patient outcomes

##### Intensive Care Delirium Screening Checklist (ICDSC)

The ICDSC is an 8-item, delirium assessment tool for use in the ICU (1 point per item) [4]. An altered level of consciousness, along with the presence of three other symptoms, including inattention, psychomotor agitation/retardation, and disorientation are required to diagnose delirium. Scores of ≥4 out of 8 on the ICDSC are indicative of delirium (Sensitivity: 99%; Specificity: 64%) [4]. The ICDSC yields both a continuous measure of symptoms and a dichotomous diagnosis of delirium. The ICDSC is completed twice daily by on-duty bedside nurses as part of standard care.

### Statistical analysis plan

All data will be analyzed as intention to treat. Descriptive statistics will be used to summarize the patient and family characteristics. For all analyses, we will consider a two-tailed *p*-value < 0.05 to be statistically significant, and will adjust for multiple comparisons (Bonferroni correction) in the primary analysis where appropriate. For the secondary aims, we will not correct for multiple comparisons with statistical procedures, but rather consider them in our interpretation. Subgroup analyses and a priori *covariates* to be considered are: presence of mechanical ventilation, RASS score, delirium subtype, patient frailty status (based on Clinical Frailty Scale scores), patient age, patient sex, caregiver age, caregiver sex, and baseline levels of symptoms of depression, anxiety, and psychological distress. Linear regression models will be used to assess for effect modification and confounding. Missing data will be tabulated for all outcomes. If more than 5% of outcome data is missing, multiple imputation will be employed; for the primary aim, we will also conduct a sensitivity analysis assuming the data is missing not at random.

For the primary aim, we will report a difference in proportion of the clinically significant symptoms of depression [PHQ-9] and anxiety [GAD-7], mean PHQ-9 and GAD-7 scores, and frequency of categories of depression and anxiety (i.e., minimal, mild, moderate and severe) (at discharge from ICU, 1-, and 3- month follow-up) between control and intervention groups. For secondary aims we will report: 1) A difference in proportion of the most severe family members symptoms of psychological distress [K-10] (at discharge from ICU, 1-, and 3- month follow-up) between control and intervention groups. 2) Prevalence of delirium: Difference in proportion of patients with clinical delirium (ICDSC score ≥ 4) pre-post intervention (in-ICU) between control and intervention groups. Duration of delirium: Difference in mean days with clinical delirium (ICDSC score ≥ 4) pre-post intervention between control and intervention groups (in-ICU). Duration of delirium-free days: Difference in mean days without delirium on the ICDSC pre-post intervention between control and intervention groups (in-ICU). Severity of delirium: Difference in most severe ICDSC scores pre-post intervention between control and intervention groups (in-ICU). 3) Difference in the diagnosis of delirium in the medical chart, compared to usual care (when appropriate, i.e., when delirium is present) pre-post intervention between control and intervention groups (in-ICU). 4) Difference in mean CIDKQ scores pre-post intervention between control and intervention groups (in-ICU). 5) Difference in mean DEL-B scores pre-post intervention between control and intervention groups (in-hospital). The statistical significance of the differences between proportions or means (between the intervention and control groups) will be calculated using the.

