#### Sample size calculation

*Primary Outcome:* To find a difference in the mean score on the PHQ-9 or GAD-7 of 3-points (from 13 to 10), with a standard deviation of 5-points, power of 90%, an alpha level of 0.05, and 20% loss to follow-up (based off of previous mortality rates in the study ICUs [local data]), 72 dyads per group are required (*N* = 144). *Secondary Outcomes:* To find a difference in the proportion of delirium events reported in the medical chart (most conservative estimate based on secondary outcomes selected) of 20% (from 10 to 30%) at 90% power, an alpha level of 0.05, and 20% loss to follow up, 99 dyads per group are required (*N* = 198). The primary outcome requires a smaller sample size, and thus the most conservative number based on a secondary outcome is employed here.

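### Bonferroni is valid for the primary comparisons, but Holm's step-down procedure gives the same familywise error control, never rejects less, and adds some power for second and later findings

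*Protocol article*

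**What the plan says.** The Statistical analysis plan section sets the general criterion: "we will consider a two-tailed *p*-value < 0.05 to be statistically significant". For the primary aim it adds that the trial "will adjust for multiple comparisons (Bonferroni correction) in the primary analysis where appropriate". For the rest, "For the secondary aims, we will not correct for multiple comparisons with statistical procedures". The article does not state how many primary comparisons are counted. It lists two scales (PHQ-9 and GAD-7), each reported as a proportion, a mean and a set of severity categories, at ICU discharge, 1 month and 3 months.

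The Sample size calculation section sizes the primary outcome for "a difference in the mean score on the PHQ-9 or GAD-7 of 3-points (from 13 to 10", "with a standard deviation of 5-points", with "power of 90%, an alpha level of 0.05, and 20% loss to follow-up". This gives 72 dyads per group. The trial adopts the larger 99 per group, which comes from a secondary outcome. No correlation between the two scales is given.

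**The concern.** The primary aim concerns depression and anxiety, so a reader will want to know about both scales. Bonferroni tests each of m comparisons at 0.05/m, whatever the others show. Holm orders the p-values and tests the smallest at 0.05/m, the next at 0.05/(m − 1), and so on, stopping at the first failure. With two scales, once one is significant at 0.025 the other is tested at the full 0.05.

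The two procedures differ when one p-value is at or below 0.025 and the other lies between 0.025 and 0.05. Bonferroni then declares one effect and Holm declares both. Familywise error control is the same, so the tests themselves gain nothing in error control from the more conservative second step. What is at stake is some power for second and later primary findings, with no change in patients or data.

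**Working it through.** **Inputs.** From the article: difference 3 points, SD 5, two-sided alpha 0.05, power 90%, loss 20%, 1:1 allocation, 99 dyads per group. Assumed, because the article gives no figure: correlation ρ between test statistics of 0 to 0.9, and a family of m = 2 (two scales) or m = 6 (two scales by three times).

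**1. The plan's own figure.** n = 2(1.960 + 1.282)² × 5²/3² = 58.4, so 59 per group. Allowing for 20% loss gives 59 × 1.2 = 71 or 59/0.8 = 74. The stated 72 is reproduced within rounding and convention.

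**2. Evaluable number.** 99 × 0.8 = 79.2, so 79 per group.

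**3. Power per test under Bonferroni.** The expected test statistic is 3/(5 × √(2/79)) = 3.771.
- m = 2, alpha 0.025, critical value 2.241: Φ(3.771 − 2.241) = 93.7%.
- m = 6, alpha 0.0083, critical value 2.638: Φ(3.771 − 2.638) = 87.1%.
- For reference, at alpha 0.05, critical value 1.960: Φ(3.771 − 1.960) = 96.5%.

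**4. Hand check of Holm at m = 2, ρ = 0.** Holm rejects both when both p-values are at most 0.05 and at least one is at most 0.025: 0.9649² − (0.9649 − 0.9369)² = 0.9310 − 0.0008 = 93.0%. Bonferroni rejects both with probability 0.9369² = 87.8%.

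**5. Simulation.** 300,000 draws of equally correlated normal test statistics, each with mean 3.771.

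Two scales, effect on both (%):

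| ρ | At least one, either method | Per scale, Bonferroni | Per scale, Holm | Both, Bonferroni | Both, Holm |
|---|---|---|---|---|---|
| 0 | 99.6 | 93.7 | 96.4 | 87.9 | 93.1 |
| 0.5 | 98.3 | 93.7 | 95.9 | 89.1 | 93.5 |
| 0.7 | 97.4 | 93.7 | 95.6 | 90.0 | 93.9 |
| 0.9 | 95.9 | 93.7 | 95.2 | 91.5 | 94.5 |

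Six tests, effect on all (%):

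| ρ | At least one, either method | Per test, Bonferroni | Per test, Holm | All six, Bonferroni | All six, Holm |
|---|---|---|---|---|---|
| 0 | 100.0 | 87.1 | 95.6 | 43.7 | 79.7 |
| 0.5 | 99.3 | 87.1 | 93.8 | 61.6 | 84.6 |
| 0.7 | 97.8 | 87.1 | 92.9 | 68.6 | 87.3 |
| 0.9 | 94.3 | 87.1 | 91.6 | 77.6 | 89.9 |

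**6. Where nothing is gained.** The chance of at least one rejection is the same, because both methods compare the smallest p-value with 0.05/m. If only one of two scales responds, power for it is 93.7% with Bonferroni and 93.8% with Holm.

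**7. Error rate.** With no effect on any scale, familywise error is identical under the two methods: at m = 2 from 4.9% (ρ = 0) to 3.6% (ρ = 0.9), and at m = 6 from 4.9% to 2.1%.

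**The case against.** The best defence is that nothing here is an error. Bonferroni is valid under any dependence, prespecified and conventional. For two scales at alpha 0.025 the requirement is 2(2.241 + 1.282)² × 25/9 = 69 evaluable per group. That is 69/0.8 = 87 recruited per group, or 174 in all, below the planned 198. Power per scale is 93.7%, above the 90% target. All of this stands, so a reader who infers that the Bonferroni choice leaves a two-scale primary analysis underpowered, or must be corrected, goes beyond the documents.

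Three further readings are tempting and unsupported:
- **Holm has more power in every sense.** It does not. Power for at least one finding is equal, and the gain is negligible when one scale responds.
- **Close correlation between the scales strengthens the case.** The article gives no correlation, Holm does not use it, and the gain per scale shrinks from about 2.6 points at ρ = 0 to 1.5 at ρ = 0.9.
- **The large contrast for all six tests measures a loss to this trial.** It needs a six-test family, the full effect at every time, and a success rule requiring all six. The article states none of these. Its sizing sentence refers to one scale or the other, and no section makes success depend on both.

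Two practical objections also hold. Bonferroni has simple simultaneous intervals that match its tests, and Holm does not. Holm also needs a defined family just as Bonferroni does, so the change does not settle which comparisons are counted, and it leaves the undivided alpha of 0.05 in the sample size calculation as it is. The full analysis plan, not shown, may specify the procedure further.

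**Conclusion.** The point holds as an optional improvement. At 79 evaluable per group, with the plan's effect assumed on both scales and ρ from 0 to 0.9, Holm raises power for both scales from 88–92% to 93–95%, and power per scale from 94% to 95–96%. Under a six-test family with all effects present, power per test goes from 87%, below the 90% the plan aims for, to 92–96%, above it, with no added dyads. That last result depends on an assumed family. The gains vanish if the effect is confined to one scale. The figures also rest on normal test statistics with equal correlations and on the planned 20% loss.

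**What to change.** Before the analysis, in the Statistical analysis plan section, replace the Bonferroni correction with the Holm step-down procedure for the primary comparisons. Report Holm-adjusted p-values, and give unadjusted 95% confidence intervals labelled as such.

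The cost is a wording change, with no new data, patients or assessments. The downside is that intervals and decisions may disagree. If both p-values lie between 0.025 and 0.05, for example, both unadjusted intervals exclude zero but Holm rejects neither hypothesis. The text should say that the significance decision rests on the Holm-adjusted p-values. If intervals that match the tests matter more to the team than a few points of power on the second scale, keeping Bonferroni is defensible.
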